### Outcomes

The primary outcome is symptomatic COVID-19, defined by the presence of at least one COVID-19-like symptom as listed in Participants section and confirmed by a positive RT-PCR result for SARS-CoV-2 infection from participants’ NP or nasal swabs.

Secondary outcomes are: (1) symptomatic SARS-CoV-2 infection associated with circulating variants (e.g., Delta, and Omicron); (2) duration of COVID-19 symptoms; (3) hospitalization for COVID-19 within 30 days from enrollment among patients with confirmed COVD-19; (4) need for ICU admission within 30 days from enrollment among patients with confirmed COVD-19; (5) need for invasive mechanical ventilation within 30 days from enrollment among patients with confirmed COVD-19; (6) death from COVID-19 within 90 days from enrollment among patients with confirmed COVD-19; (7) health-related quality of life at 90 days from enrollment among patients with confirmed COVD-19, measured by the three-level version of the EuroQol five-dimensional descriptive system (range, -0.17 [worst] to 1.0 [best]; minimal important difference, 0.03) [7, 8]; (8) persistent COVID-19 symptoms at 180 days from enrollment among patients with confirmed COVD-19; (9) symptomatic SARS-CoV-2 reinfection within 365 days from enrollment among patients with confirmed COVD-19, defined as recurrence of COVID-19-like symptoms confirmed by a positive RT-PCR or antigen test for SARS-CoV-2 more than 90 days after primary infection.

Safety data including adverse events and serious adverse events will be assessed upon inclusion of cases and controls and over the 12-month follow-up for cases, under the standard of care procedures for the city of Toledo’s surveillance program per Brazilian regulatory authority’s requirements.

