### Study setting

This study has been conducted in Toledo (24° 42′ 50″ S, 53° 44′ 34″ W), a city in the state of Paraná, southern Brazil. The population of Toledo was estimated at 144,601 people in 2021. As of 05 February 2022, COVID-19 has affected 38,614 people with 478 deaths. The city secretary of health initiated an age-based COVID-19 vaccination campaign on 20 January 2021, starting with adults 16 years of age and older. A mass vaccination campaign using BNT162b2 for all nonimmunized individuals aged ≥ 12 years was initiated on 27 August 2021 using a two-dose schedule administered 21 days apart. A third dose (i.e., booster dose) of BNT162b2 has been recommended for healthy (according to an age-based prioritization strategy) and immunocompromised individuals aged ≥ 12 years since 15 September 2021. Other available COVID-19 vaccines in Toledo include CoronaVac (Sinovac), ChAdOx1 nCoV-19 (AstraZeneca), and Ad26.COV2.S (Janssen); around 50% of the vaccine-eligible individuals immunized against COVID-19 have received BNT162b2.

Toledo was chosen due to the city standard of care, which provides free healthcare access to a wide variety of COVID-19 diagnosis and management services, and due to the feasibility of accessing information on people who were tested for SARS-CoV-2 through the city surveillance system.

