#### Handling missing data

No data imputation will be performed for main exposure (vaccination status) and for the study outcome. Main analysis will consist of observed data, without imputation. For sensitivity analysis we will perform multiple imputation if missing data on core variables is > 5%, under the assumption that the missingness pattern is missing at random conditional on the observed data. Core variables are defined as the covariates to be used in the primary analysis: age, gender, Charlson comorbidity index [18], current smoking status, and body mass index (BMI) category.

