#### Secondary outcome analyses

The association between the exposition variables with symptomatic SARS-CoV-2 infection caused by circulating variants as well as the association between secondary exposition variables with symptomatic SARS-CoV-2 infection will be assessed using the same statistical model used for the primary outcome.

Crude and adjusted generalized linear models will be used to assess the impact of exposures on duration of COVID-19 symptoms, hospitalisation for COVID-19, need for ICU admission, need for invasive mechanical ventilation, death from COVID-19, health-related quality of life, persistent COVID-19 symptoms, symptomatic SARS-CoV-2 reinfection among participants with a positive RT-PCR result for SARS-CoV-2, and to test associations between length of time after receipt of the second or third dose of BNT162b2 and the risk of symptomatic SARS-CoV-2 infection, according to the probability distribution of each outcome. Quantitative outcomes will be expressed as mean difference. Categorical outcomes will be expressed as hazard ratio or relative risk as appropriate.

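### The 90-day EQ-5D comparison is defined for all confirmed cases but, as written, compares only survivors, which favours whichever exposure group has more deaths

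*Protocol article*

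**What the plan says.** All statements are in the protocol article.

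- **Outcomes.** Secondary outcome 7 is "health-related quality of life at 90 days from enrollment among patients with confirmed COVD-19", measured by EQ-5D-3L on a scale from -0.17 to 1.0, with "minimal important difference, 0.03". Secondary outcome 6, in the same population and at the same horizon, is "death from COVID-19 within 90 days from enrollment among patients with confirmed COVD-19". Outcome 8 is persistent symptoms at 180 days, again among confirmed cases.
- **Data collection.** Cases are followed by structured telephone interview, including at 3 and 6 months.
- **Handling missing data.** "No data imputation will be performed for main exposure (vaccination status) and for the study outcome". The section adds that the main analysis consists of observed data.
- **Secondary outcome analyses.** "Crude and adjusted generalized linear models will be used to assess the impact of exposures" on these case-only outcomes, and "Quantitative outcomes will be expressed as mean difference".
- **Overall principles.** Secondary analyses are not adjusted for multiplicity and are to be read as exploratory.
- **Study setting.** The only mortality figure is city-wide, to 5 February 2022: "COVID-19 has affected 38,614 people with 478 deaths".

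The article gives no utility value for death and no other rule for cases who die before the interview.

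**The concern.** A case who dies before day 90 cannot be interviewed and so has no utility. Under an observed-data analysis that case drops out. The outcome is defined for all confirmed cases, but the people compared are the surviving ones who were interviewed.

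Death by day 90 is itself something the vaccine may affect; objective 6 asks exactly that. Restricting to survivors therefore conditions on a possible consequence of exposure. If deaths differ by vaccination group, the worst outcomes are removed unequally and the mean difference no longer answers objective 7 for all cases. Model adjustment does not bring the dead back into the comparison. Persistent symptoms at 180 days have the same structure.

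At stake is the reading of one exploratory secondary result, not the primary vaccine effectiveness estimate.

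**Working it through.** **The plan's own figures.** The article gives no sample size or power for quality of life, so there is none to reproduce for this outcome. The primary calculation does reproduce, and it supplies a vaccinated share for cases. With odds ratio 0.20 and 90% coverage in controls, coverage in cases is 0.20 × 0.90 / (0.10 + 0.20 × 0.90) = 0.643. With 622 cases and 1,244 controls the standard error of the log odds ratio is 0.1262, and the 95% interval for effectiveness is 74.4% to 84.4%, a width of 9.998 points against the stated 10.

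**Formula.** Let d be the proportion dead by day 90 and m the mean utility in survivors (v = vaccinated, u = unvaccinated).

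- Survivor-only difference: m_v − m_u
- Difference with deaths scored 0: (1 − d_v)m_v − (1 − d_u)m_u
- Shift (second minus first): m_u·d_u − m_v·d_v, which is m(d_u − d_v) when the survivor means are equal

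**Inputs.** City fatality is 478/38,614 = 1.238% (Study setting). The minimal important difference is 0.03 (Outcomes). The following are assumptions, because the article does not give them: survivor utility m = 0.85 in both groups, death ratio r = d_v/d_u of 0.2 to 0.5, and vaccinated share of cases p of 0.50 to 0.66 (the 0.643 above lies in this range).

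**Reading A: 1.238% is the risk in unvaccinated cases.** Shift = 0.85 × 0.01238 × (1 − r).

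**Reading B: 1.238% is the overall risk in cases.** Then d_u = 0.01238 / (p·r + 1 − p), and shift = 0.85 × d_u × (1 − r).

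| Reading | p | r | d_u | d_v | Shift | Share of 0.03 |
|---|---|---|---|---|---|---|
| A | – | 0.5 | 1.24% | 0.62% | 0.0053 | 18% |
| A | – | 0.2 | 1.24% | 0.25% | 0.0084 | 28% |
| B | 0.50 | 0.5 | 1.65% | 0.83% | 0.0070 | 23% |
| B | 0.66 | 0.5 | 1.85% | 0.92% | 0.0079 | 26% |
| B | 0.50 | 0.2 | 2.06% | 0.41% | 0.0140 | 47% |
| B | 0.66 | 0.2 | 2.62% | 0.52% | 0.0178 | 59% |

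**Sign.** Under reading A, r = 1 gives a shift of 0. With r = 2, the shift is 0.85 × 0.01238 × (1 − 2) = −0.0105: the survivor-only mean then flatters the vaccinated group.

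**What would reach 0.03.** The death difference would have to be 0.03/0.85 = 3.5 percentage points, or 3.0 points if survivor utility were 1.0.

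No size is calculated for the 180-day outcome, because the article gives nothing on which to base one.

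**The case against.** **The exclusion is not stated.** The missing-data section speaks of one study outcome, in the singular, and may mean only the primary one. Giving death a fixed value is arguably part of defining the outcome and not imputation. A full analysis plan, not shown here, may hold such a rule. This stands as a limit on certainty. It does not remove the point: the sentence on observed data is general, the utility comes from a telephone interview, and the article gives no other rule for this outcome.

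**Deaths are not hidden.** Mortality is reported at the same horizon in the same population, and secondary analyses are exploratory. This limits the consequence. It does not repair the contrast, because an unlabelled mean difference would still be read as the vaccine's impact in all cases.

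**A reader might infer that the vaccine's effect is understated.** The article does not support this. It gives no deaths by vaccination group. The campaign was age-based, and boosters followed age priority and were also recommended for immunocompromised people, so vaccinated cases could be older or sicker and could die more often. The direction would then reverse.

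**The fatality figure is weak.** It is cumulative for the city and includes the time before the mass BNT162b2 campaign of 27 August 2021 and the first enrolment on 3 November 2021. It is not specific to study cases, vaccination group or 90 days. The upper part of the range arises only under reading B. This stands, and the size must be read as conditional.

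**Survivor quality of life beside mortality is a legitimate presentation.** Agreed. Resting the objective-7 conclusion on the death-scored mean would be a different choice of estimand, and the documents do not compel it.

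**Conclusion.** The point holds in a limited form. The article's rules, taken together, turn an outcome defined for all confirmed cases into a survivor-only comparison without saying so, and that comparison favours the exposure group with more deaths. Whether a vaccine benefit is understated, overstated or unaffected depends on deaths by group, which are not given.

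With the city fatality, death ratios of 0.2 to 0.5 and survivor utility of 0.85 as assumptions, the shift is about 0.005 to 0.018, or 18% to 59% of the minimal important difference. Every scenario tabulated stays below 0.03, so the calculation does not show that deaths alone would create or hide an important difference. The shift can still be a material part of one. It would be smaller if fatality among study cases is lower than the city figure. The consequence is confined to exploratory secondary outcomes.

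**What to change.** 1. Label the planned 90-day EQ-5D mean difference as survivor-only.
2. Beside it, report a sensitivity analysis that scores participants who died by day 90 as 0, a value inside the stated -0.17 to 1.0 scale, and show 90-day mortality by exposure group in the same table.
3. For 180 days, report death or persistent symptoms beside persistent symptoms in survivors.

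The cost is a few lines of analysis-plan wording and one extra analysis per outcome. The 90-day analysis uses an outcome already collected. The defined death outcome covers deaths from COVID-19 to day 90, so the wording should say how deaths from other causes, and deaths between days 90 and 180 learned through continuing follow-up, are counted. The downside is that a death-scored mean is slightly harder to interpret clinically. It should therefore supplement the survivor-only estimate and not replace it.

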### Sample size

The sample size was calculated based on formulas published by O’Neill RT [9]. Assuming the recruitment of two controls per case, a vaccine coverage rate of 90% among controls, a sample of 622 cases and 1,244 controls will be required to detect a vaccine effectiveness of 80% with a precision width of 10%. Considering that around 50% of enrolled participants will fulfil criteria for the primary analysis (≥ 2 doses of BNT162b2 or unvaccinated) and increasing the sample size by 20% (due to parameter uncertainties, potential COVID-19 misclassifications, and need for covariate adjustment), the study will need to include 1,500 cases and 3,000 controls.

### Data collection

The schedule of enrollment and assessment is detailed in Fig 2. Controls are evaluated at a single point in time (baseline). Cases are evaluated at baseline and then followed up for 12 months by means of structured telephone interviews at 15 days, and at 1, 3, 6, 9 and 12 months after inclusion in the study.

**Fig 2 pone.0276384.g002:**
[figure not shown]
Schedule of enrollment and assessment. N/A. Not appliable; RT-PCR, reverse transcriptase polymerase chain reaction.

Baseline assessment is performed by trained researchers at each participating site at the time an eligible participant with symptoms of COVID-19-like illness seeks care through the public healthcare system. The vaccination status is assessed through structured interviews and adjudicated through review of city medical registry records reviews. Telephone follow-up is conducted via a single central telephone system located in the study coordinating centre (Hospital Moinhos de Vento). Therefore, all participants who are eligible for telephone follow-up (cases), regardless of the site of inclusion, are followed up by researchers trained in good clinical practices and in standardized telephone interview methods. The reference date for scheduling telephone interviews is the date of inclusion in the study. Interviews are considered lost if the participants’ telephone lines are disconnected or non-existent or after 10 attempts at different times on several days within a 5-day time window (5 days after the estimated interview date) for the 15-day interview, and 15-day time window (15 days after the estimated interview date) for the 1-, 3-,6-,9-, and 12-month interviews. Regardless of whether an interview is lost or not, contact is attempted at the subsequent scheduled interviews. This follow-up methodology has been used in previous observational studies [10, 11].

The data are collected using smartphone-, tablet- or computer-based electronic case report forms available on the *Otus* platform (https://site.otus-solutions.com.br/). Access to databases on this platform are granted only by the principal investigator to research team members through a personal, non-transferable username and password. An encrypted digital certificate is used to ensure security in data handling. Platform users (team members) have specific permissions related to their role in the study.

The following procedures have been performed to ensure the quality of the data collected: (1) all researchers have received training in good clinical practices and study procedures, including data collection, before the start of the study; (2) trained personnel at the participating sites are able to contact the study coordinating centre to resolve any questions or problems that they might have; (3) the database is backed up automatically every 12 hours; (4) telephone interviews are recorded and audited to verify data consistency, and the audio files are stored on a server following the same security standards as for the *Otus* platform database; (5) data cleaning is conducted periodically to identify potential inconsistencies in data sets, in which case the researchers are notified for correction; and (6) the coordinating centre have been performing remote monitoring of data quality, revision of detailed reports on screening, inclusion, follow-up, data consistency and completeness on a monthly basis, taking immediate action to resolve any issues, and have been using statistical techniques for identifying fraud throughout the study.

### Collection of biological samples, and diagnostic procedures

A NP or nasal swab sample is collected from all participants for SARS-CoV-2 RT-PCR test and identification of the implicated genetic variant of SARS-CoV-2 at the time of enrollment. This collection is performed by a trained healthcare provider as part of the local policy for surveillance of individuals with suspected or confirmed diagnosis of COVID-19.

All biological materials collected in the study are transported, stored and processed by the Federal University of Paraná (UFPR) according to standardized protocols. NP or nasal swabs are stored in 15 mL falcon tubes containing viral transport medium (VTM) at -80°C, until RT-PCR testing for SARS-CoV-2 and identification of the genetic variants of SARS-CoV-2 are performed.

#### RT-PCR procedures

Total RNA is extracted from the specimens using a viral RNA and DNA kit (MVXA-P096FAST) in an automatic nucleic acid extractor (Extracta 32, Loccus Biotecnologia, Brazil), using magnetic beads. The specimens are then tested to confirm the presence of SARS-CoV-2 genetic material using the BIOMOL OneStep/COVID-19 KIT (IBMP, Curitiba, Brazil) or using the Centers for Disease Control and Prevention 2019-Novel Coronavirus (2019-nCoV) Real-Time RT-PCR Diagnostic Panel (https://www.fda.gov/media/134922/download). This approach has demonstrated high specificity (100%) and sensitivity (88% to 98%) for COVID-19 diagnosis [12, 13].

#### Variant identification

All confirmed positive samples are screened for mutations by RT-PCR to detect SARS-CoV-2 variants as follows: Initially, the multiplex RT-PCR method is performed to detect the Spike Δ69–70 and ORF1a Δ3675–3677 deletions for distinguishing Alpha, Beta/Gamma, wild type/Delta, and Omicron variants (Table 1) [14, 15]. Secondly, the predicted variant is confirmed by two allelic discrimination TaqMan assays (ThermoFisher, USA), which include: K417T, K417N, N501Y, P681R, G339D (Table 2). These assays allow to identify the variants of concern: Alpha (N501Y), Beta (K417N, N501Y), Gamma (K417T, N501Y), Delta (P681R), Omicron BA.1 (N501Y, G339D), and Omicron BA.2 (N501Y, G339D, K417T/N).

**Table 1 pone.0276384.t001:** Interpretation of the multiplex RT-PCR for Spike del69/70, Orf1a and N gene.

Spike Del69/70	Orf1a Del3675/3677	N gene	Putative variant
ND	ND	+	Alpha
+	ND	+	Beta/Gamma/BA.2
+	+	+	Wild-type/Delta
ND	+	+	Omicron BA.1

ND: non detected (cycle threshold [CT] value ˃ 40.0); +: positive (CT value ≤ 40.0).

**Table 2 pone.0276384.t002:** Identification of SARS-CoV-2 variants by two allelic discrimination assays.

Multiplex assay indication	Two allelic discrimination TaqMan assay	RT-PCR Results	Variant detected
Alpha	K417T	K417T: wt	Alpha
	N501Y	N501Y: mut	
Beta/Gamma/Omicron BA.2	G339D	G339D: wt	Beta
	K417T/N	K417N: mut	
	N501Y	N501Y: mut	
		G339D: wt	Gamma
		K417T: mut	
		N501: mut	
		G339D: mut	Omicron BA.2
		K417T/N: wt	
		N501Y: mut	
Wild/Delta	N501Y	N501Y: wt	Wild-type
	P618R	P681R: wt	
		N501Y: wt	Delta
		P681R: mut	
Omicron BA.1	G339D	G339D: mut	Omicron BA.1
	N501Y	N501Y: mut	

wt: wild-type allele amplification; mut: mutated allele amplification. Any different profile will be classified as “inconclusive”.

Assays are performed using the GoTaq Probe 1-Step RT-qPCR System (Promega) in a 7500 Fast or QuantStudio5 real-time thermocycler (ThermoFisher Scientific Inc., USA), as described by Adamoski et al [16].

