## Study status

The study design and protocol were finalised in October 2021. The first participant was included on November 3, 2021. At study start, approximately 2/3 of the target population was fully vaccinated. Two thousand and thirty-four participants were enrolled up to February 2, 2022. Currently, this study is recruiting participants in 3 referral COVID-19 sites in Toledo. We anticipate that the recruitment will be completed in July 2022.

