### Protocol review and amendments

#### Sample size review

According to the original sample size estimation, 2,979 participants (993 cases and 1,986 controls) would be required to detect an odds ratio ≤ 0.70 for the primary outcome analysis, assuming the recruitment of two controls per case, a rate of complete vaccination with the Pfizer-BioNTech BNT162b2 mRNA vaccine of 60% in the control group, a two-tailed alpha of 5%, a power of 80%, and an increased sample size by 30% (due to parameter uncertainties and need for covariate adjustment). In order to achieve adequate power to assess the impact of BNT162b2 on symptomatic SARS-CoV-2 infection associated with the Gamma variant (predominant SARS-COV-2 lineage at the time of study protocol development), considering a rate of 32.5% of genotyping tests with inconclusive results and a prevalence of 90% of the Gamma variant, the original sample size was determined to be 4,500 participants (1,500 cases and 3,000 controls).

In January 2022, the study sample size was revised, given the frequent variation of COVID-19 pandemic factors that could impact sample size estimation (e.g., emergence of Omicron variant, scarcity of new COVID-19 cases due to Gamma variant, increase in vaccine coverage, and vaccine effectiveness variations for distinct SARS-CoV-2 variants). Revision was made based solely on the number of recruited patients, number of cases and proportion of positive cases in the whole sample, without any additional analysis. The original study sample size (4,500 participants) was judged to provide an appropriate power to assess the primary outcome analysis as described in the sample size section.

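### The Alpha confirmation row omits G339D, so an Omicron BA.1 sample whose ORF1a target fails can be confirmed as Alpha instead of being classed inconclusive

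*Protocol article*

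**What the plan says.** The section Variant identification sets out two steps. A multiplex RT-PCR reads Spike, ORF1a and the N gene and gives a putative variant (Table 1). Then "the predicted variant is confirmed by two allelic discrimination TaqMan assays", with the assays depending on the prediction (Table 2).

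- Table 1 assigns Alpha to Spike not detected, ORF1a not detected, N positive. The BA.1 row is "ND + + Omicron BA.1".
- The Table 1 footnote gives "ND: non detected (cycle threshold [CT] value ˃ 40.0" as the meaning of non-detection.
- The text lists the identifying mutations as "Alpha (N501Y), Beta (K417N, N501Y), Gamma (K417T, N501Y), Delta (P681R), Omicron BA.1 (N501Y, G339D".
- Table 2 confirms Alpha on K417T wild-type and N501Y mutant. It confirms BA.1 on G339D mutant and N501Y mutant. G339D is run in the BA.1 and Beta/Gamma/BA.2 branches only.
- The safeguard under Table 2 is "Any different profile will be classified as “inconclusive".

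The outcome that uses these calls is the first secondary outcome, "symptomatic SARS-CoV-2 infection associated with circulating variants (e.g., Delta, and Omicron". It is analysed with the primary logistic model (Secondary outcome analyses).

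**The concern.** A confirmatory step should be able to contradict the prediction it follows. In Table 1 one target decides between Alpha and BA.1, and a deleted target and a failed one give the same reading. The Alpha branch then asks for two results that, on the text's marker list, Alpha and BA.1 share. An error in ORF1a therefore passes through confirmation unchallenged.

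The result would be a wrong named variant, not a missing one. Such a case leaves the Omicron analysis, is not counted as a genotyping failure, and adds to an Alpha group that may not be real. The Introduction calls Omicron the most prevalent lineage at the time of writing, and the Discussion presents genotyping of all cases as a strength that permits variant-specific effectiveness. For recruitment, Study status says "We anticipate that the recruitment will be completed in July 2022".

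**Working it through.** **Inputs.** Tables 1 and 2, the marker list and the two footnotes, all from Variant identification. Two readings are inferred. BA.1 is taken as wild-type at K417T because the list does not give it that mutation; Table 2 reports no 417 result for BA.1. Beta (K417N) is taken to read wild-type on the K417T assay.

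**Classification check.** Each variant is followed through both tables, with the allelic assays assumed to work and N positive.

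| Sample | Failed target | Table 1 prediction | Table 2 result |
|---|---|---|---|
| BA.1 | none | BA.1 | BA.1 |
| BA.1 | ORF1a | Alpha | **Alpha** |
| BA.1 | Spike | BA.1 | BA.1 |
| BA.2 (417 wild-type, as in Table 2) | none | Beta/Gamma/BA.2 | BA.2 |
| BA.2 (417 wild-type, as in Table 2) | Spike | Alpha | **Alpha** |
| Delta | ORF1a | Beta/Gamma/BA.2 | inconclusive |
| Delta | Spike | BA.1 | inconclusive |
| Wild-type | ORF1a | Beta/Gamma/BA.2 | inconclusive |
| Gamma | Spike | Alpha | inconclusive (K417T mutant) |
| Beta | Spike | Alpha | Alpha |

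For Delta and wild-type the second step catches the failed target. For BA.1 it does not: K417T wild-type with N501Y mutant is itself the listed Alpha profile, so the inconclusive rule never applies.

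**Effect on Omicron VE.** Let f be the share of Omicron cases relabelled Alpha, separately in vaccinated and unvaccinated cases. Relabelled cases leave the case group and the controls do not change, so for the crude odds ratio (OR):

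OR observed = OR true × (1 − f vaccinated) / (1 − f unvaccinated), and VE = 1 − OR.

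The article gives no f. The rates below are assumptions that show direction and scale only.

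| f vaccinated / f unvaccinated | True VE 80% | True VE 50% |
|---|---|---|
| 5% / 5% | 80.0% | 50.0% |
| 20% / 20% | 80.0% | 50.0% |
| 10% / 5% | 81.1% | 52.6% |
| 20% / 10% | 82.2% | 55.6% |
| 30% / 10% | 84.4% | 61.1% |

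Example: 0.20 × 0.90 / 0.95 = 0.1895, so VE = 81.1%. Equal failure leaves VE where it was and costs only cases.

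**Check of the proposed row.** If Alpha also requires G339D wild-type, BA.1 with a failed ORF1a target gives G339D mutant and no longer matches. BA.2 with a failed Spike target is excluded in the same way. True Alpha, listed without G339D, is still confirmed.

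**The case against.** The strongest objection is that a key premise is inferred. The article lists the mutations used to identify BA.1 and is silent on its 417 result. It also conflicts with itself on 417 for BA.2: the text gives K417T/N, while Table 2 requires wild-type. If BA.1 did not give a clean wild-type K417T call, the sample would be inconclusive, as intended. This stands as a condition on the point.

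Second, the path is narrow. ORF1a must exceed CT 40 while N does not, and both allelic assays must still give clean calls on the same sample. A low viral load that defeats ORF1a could also defeat them, and the sample would then be inconclusive. This stands too, and it limits the likely number.

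Third, laboratory handling is condensed here. The article refers to standardized protocols and cited assay methods, which may contain repeat-testing rules for weak samples. That is possible, but the article states the Alpha row and its required profile explicitly, and the row as stated has the gap.

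Three stronger readings are tempting, and the documents do not support them.

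- A reader might take "considering a rate of 32.5% of genotyping tests with inconclusive results" as a measure of how many cases are affected. It is an inconclusive rate from the sample size set when Gamma was predominant. It describes samples left without a variant, not samples given the wrong one, and it is not a target-failure rate.
- A reader might infer that Omicron VE is biased. That needs failure to differ by vaccination status, for which the article offers no evidence.
- A reader might infer that later lineages lacking both targets would all be called Alpha. The article describes no such lineage.

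**Conclusion.** The gap is real but conditional. On the article's own markers, the Alpha row cannot contradict a false Alpha prediction that arises from BA.1 with a failed ORF1a target, or from BA.2 as Table 2 profiles it with a failed Spike target. This rests on 417 reading wild-type in those samples and on N and both allelic assays working. The multiplex step does separate Alpha from BA.1 whenever ORF1a amplifies, so this is not a general failure to tell the two apart.

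The number of cases cannot be computed from the document. The consequence is confined to the variant-specific secondary outcome, which Overall principles declares exploratory: fewer Omicron cases, some loss of precision, and bias only under differential failure. The primary outcome counts any RT-PCR-positive symptomatic case and is unaffected. The change is worth making because it is cheap and removes a wrong named call, not because the main result is at risk.

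**What to change.** Add G339D to the Alpha row of Table 2, and require G339D wild-type, K417T wild-type and N501Y mutant for Alpha. Class samples with Spike and ORF1a both undetected and G339D mutant as Omicron, sublineage undetermined, or as inconclusive. State which before analysis. Re-run stored samples already called Alpha where material remains.

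Add G339D; do not substitute it for K417T. K417T is what now excludes Gamma with a failed Spike target. After a swap, that sample would read G339D wild-type and N501Y mutant and be confirmed as Alpha.

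The cost is one further assay, already in the panel, on samples predicted to be Alpha. The branch would then have three assays, as the Beta/Gamma/BA.2 branch already does. One residual remains: Beta with a failed Spike target would still match Alpha. Reading 417 as K417T/N, as the Beta/Gamma/BA.2 branch does, would close it, though Beta is not among the variants the outcome names. The conflicting 417 entries for BA.2 in the text and Table 2 should be reconciled in the same edit.

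### The text and Table 2 give incompatible K417 rules for calling Omicron BA.2; if the text is right and Table 2 is applied, BA.2 cases become inconclusive and could drop out of the Omicron-specific estimate

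*Protocol article*

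**What the plan says.** All the calling rules are in the protocol article, Variant identification.

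- **Text.** Each variant of concern is followed by a bracket of mutations. The last two entries are "Omicron BA.1 (N501Y, G339D), and Omicron BA.2 (N501Y, G339D, K417T/N").
- **Table 1.** The multiplex step cannot separate BA.2 from Beta and Gamma. The shared pattern is labelled "Beta/Gamma/BA.2", so the allelic discrimination step decides the call.
- **Table 2.** In that branch, Beta and Gamma need G339D wild-type, with K417N or K417T mutated. BA.2 needs G339D mutated, N501Y mutated and K417T/N wild-type.
- **Table 2 footnote.** The codes are defined as "wt: wild-type allele amplification; mut: mutated allele amplification". The footnote then adds "Any different profile will be classified as" inconclusive.

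The calls feed the first secondary outcome (Outcomes): "symptomatic SARS-CoV-2 infection associated with circulating variants (e.g., Delta, and Omicron"). According to Secondary outcome analyses, this outcome "will be assessed using the same statistical model used for the primary outcome". That section gives no rule for inconclusive genotypes.

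**The concern.** Take a sample in the shared branch with G339D, N501Y and K417 all mutated. By the text it is BA.2. By Table 2 it fits no row, because Beta and Gamma need G339D wild-type and BA.2 needs K417 wild-type, so it is inconclusive. A sample with G339D and N501Y mutated and K417 wild-type is BA.2 by Table 2 but lacks one of the three mutations in the text.

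The call decides who counts as an Omicron case in secondary outcome 1. The Introduction describes Omicron as the dominant lineage at the time of writing, and the Discussion presents genotyping of all cases as a strength. If BA.2 samples were set aside as inconclusive, the Omicron estimate would rest on fewer cases, drawn from BA.1 alone.

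**Working it through.** No sample size, power or alpha figure is at issue, so there is no plan figure to reproduce. The check compares the text with Table 2 and then bounds the count.

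**Step 1. Text brackets against Table 2.**

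| Variant | Text bracket | Table 2: mutated | Table 2: wild-type | Bracket = mutated alleles? | Bracket = all assays in row? |
|---|---|---|---|---|---|
| Alpha | N501Y | N501Y | K417T | yes | no |
| Beta | K417N, N501Y | K417N, N501Y | G339D | yes | no |
| Gamma | K417T, N501Y | K417T, N501Y | G339D | yes | no |
| Delta | P681R | P681R | N501Y | yes | no |
| BA.1 | N501Y, G339D | G339D, N501Y | none | yes | yes |
| BA.2 | N501Y, G339D, K417T/N | G339D, N501Y | K417T/N | **no** | yes |

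(The Gamma row prints N501 without the final letter; it is read here as N501Y.)

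For five of the six variants the bracket equals the alleles marked as mutated. BA.2 is the only exception.

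**Step 2. Can the brackets be read as assays run?** That reading would remove the BA.2 conflict, but it fails for Alpha, Beta, Gamma and Delta. Each of these has an assay in Table 2 that is absent from its bracket. The brackets list mutations, and the K417 conflict is real.

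**Step 3. Which samples change?** Within the Beta/Gamma/BA.2 branch, with G339D and N501Y both mutated:

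| K417 result | Text | Table 2 with footnote | G339D + N501Y only |
|---|---|---|---|
| mutated | BA.2 | inconclusive | BA.2 |
| wild-type | not the listed profile | BA.2 | BA.2 |

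G339D alone separates BA.2 (mutated) from Beta and Gamma (wild-type) here. K417 is needed only to separate Beta from Gamma.

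**Step 4. Do inconclusive samples leave the analysis?** This is implied, not stated. Sample size review sized the variant analysis "considering a rate of 32.5% of genotyping tests with inconclusive results and a prevalence of 90% of the Gamma variant", which treats inconclusive genotypes as lost. Handling missing data rules out imputation of the study outcome.

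**Step 5. How many cases?** The documents give 1,500 planned cases (Sample size) but no BA.2 share. The shares below are assumptions for illustration. Samples at risk = 1,500 × share, if the text is right and Table 2 is applied:

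| Assumed BA.2 share | Samples at risk |
|---|---|
| 10% | 1,500 × 0.10 = 150 |
| 25% | 1,500 × 0.25 = 375 |
| 50% | 1,500 × 0.50 = 750 |
| 75% | 1,500 × 0.75 = 1,125 |

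If Table 2 is right, the loss is 0 at every share.

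**The case against.** The strongest reply is that Table 2 with its footnote is the only complete algorithm in the article and the text points to it, so the laboratory may always have followed one rule. The BA.2 bracket also names exactly the three assays of that branch and uses the combined label K417T/N, whereas Beta and Gamma each name one specific mutation. It may therefore be an assay list that slipped into a sentence about mutations. This stands as an explanation of how the text could be the slip. It does not remove the inconsistency, because the same sentence lists mutations for the other variants.

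A second objection also stands. Genotype enters neither the primary outcome nor the primary model. Overall principles calls the secondary analyses exploratory, and the outcome names Omicron as a whole, with no separate BA.1 and BA.2 estimates stated.

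A reader might infer more than the documents support:

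- **That BA.2 cases will be lost.** This needs both the text to be right and Table 2 to be the rule in use. The documents establish neither.
- **That any loss adds to the 32.5% inconclusive rate.** That rate comes from the original Gamma-based sizing, and no reasons for it are given. Whether the losses overlap or add is unknown.
- **That an estimate limited to BA.1 reflects another calendar period or vaccine mix.** Nothing in the article says so.

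An objection to the simplified rule is that it removes K417 as a confirmatory marker for BA.2, and the article gives no assay-performance data to show this is harmless. That stands as a small cost.

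**Conclusion.** The section states two incompatible BA.2 rules. This is a fault in a rule that the article sets out in full, not detail left to a longer document. The direction of the consequence is conditional: possible loss of BA.2 cases from the Omicron-specific estimate if the text is right and Table 2 is applied, and no loss if Table 2 is right. Removal from the analysis further assumes that inconclusive samples are excluded, which is implied only.

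The size cannot be derived. The range of 150 to 1,125 samples rests wholly on assumed BA.2 shares of 10% to 75% and is not an estimate. A loss would cost precision for Omicron. It would shift the estimate only if effectiveness differed between BA.1 and BA.2, on which the article gives no information. The primary effectiveness estimate is unaffected. Severity is moderate: it should be settled before the variant analysis, but it does not threaten the main result.

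**What to change.** Reconcile the text and Table 2 before the variant analysis, and state which K417 result the BA.2 rule expects. If the text is the slip, the bracket changes; if the table is, the BA.2 row changes.

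A rule that works under either version is available:

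1. In the Beta/Gamma/BA.2 branch, call BA.2 on G339D mutated plus N501Y mutated, the pair that Table 2 already uses to confirm BA.1.
2. Use K417T/N in that branch only to separate Beta from Gamma.
3. Re-code existing results under the reconciled rule where allele-level results are stored. The article does not say whether they are.
4. Report how many BA.2 calls depend on the change, since K417 no longer confirms them.
5. State how inconclusive genotypes enter the variant-specific model.

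The cost is a correction to one line of text or one table row, plus re-coding. The assays needed are already specified for this branch, so no new ones are required where allele results have been kept. Overall principles places analysis after database cleaning and lock, so the rule can be fixed before any variant-specific result is seen.
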